## Abstract

**Background:**

Uncontrolled asthma during pregnancy is associated with the maternal hazards of disease exacerbation, and perinatal hazards including intrauterine growth restriction and preterm birth. Interventions directed at achieving better asthma control during pregnancy should be considered a high priority in order to optimise both maternal and perinatal outcomes. Poor compliance with prescribed asthma medications during pregnancy and suboptimal prescribing patterns to pregnant women have both been shown to be contributing factors that jeopardise asthma control. The aim is to design and evaluate an intervention involving multidisciplinary care for women experiencing asthma in pregnancy.

**Methods/design:**

A pilot single-blinded parallel-group randomized controlled trial testing a Multidisciplinary Approach to Management of Maternal Asthma (MAMMA©) which involves education and regular monitoring. Pregnant women with asthma will be recruited from antenatal clinics in Victoria, Australia. Recruited participants, stratified by disease severity, will be allocated to the intervention or the usual care group in a 1:1 ratio. Both groups will be followed prospectively throughout pregnancy and outcomes will be compared between groups at three and six months after recruitment to evaluate the effectiveness of this intervention. Outcome measures include Asthma Control Questionnaire (ACQ) scores, oral corticosteroid use, asthma exacerbations and asthma related hospital admissions, and days off work, preventer to reliever ratio, along with pregnancy and neonatal adverse events at delivery. The use of FEV_1_/FEV_6_ will be also investigated during this trial as a marker for asthma control.

**Discussion:**

If successful, this model of care could be widely implemented in clinical practice and justify more funding for support services and resources for these women. This intervention will also promote awareness of the risks of poorly controlled asthma and the need for a collaborative, multidisciplinary approach to asthma management during pregnancy. This is also the first study to investigate the use of FEV_1_/FEV_6_ as a marker for asthma control during pregnancy.

**Trial registration:**

Australian New Zealand Clinical Trials Registry (ACTRN12612000681853)

## Background

Preterm birth and intrauterine growth restriction remain leading contributors to perinatal mortality and morbidity. Preterm birth is the leading cause of neonatal death, and over half of term stillbirths are associated with impaired fetal growth. Beyond the perinatal period, survivors of preterm birth and fetal growth restriction face a range of long term adverse health outcomes through infancy and childhood
[1], and many adult diseases are now recognised to have their origins in fetal life
[2-4]. Accordingly, continued efforts are necessary to identify interventions that may reduce the burden of preterm birth, and improve in utero fetal growth.

Poorly controlled asthma during pregnancy has been shown to be associated with an increased risk of preterm birth, low birth weight, and pre-eclampsia
[5,6]. This data suggests that improved asthma control may be a means of reducing these important perinatal outcomes and that proper asthma management among pregnant women should be regarded as a health priority. In general, they should be managed in the same way as non-pregnant women with asthma, with the exception their asthma should be monitored at least monthly, as pregnancy can have a significant effect on asthma control
[7,8]. A lack of knowledge amongst women regarding the risks of uncontrolled asthma during pregnancy is evident. Furthermore, there is a lack of confidence amongst health professionals when deciding the best management strategy for these women
[9]. These concerns need to be addressed, as a starting point to optimise asthma control during pregnancy. Strategies to improve asthma management during pregnancy are warranted.

Preventive asthma medications at regular doses have been shown to be safe to use during pregnancy and the risks of reduction or discontinuation of these medications are far worse
[10,11]. Asthma guidelines around the world strongly recommend that women continue their asthma medications during pregnancy to maintain adequate control
[7,8,12-18]. However, women are still choosing to cease their asthma medications during pregnancy, many without consulting their doctors
[19-21]. Reasons for this include concern over using any medication use during pregnancy, a desire for alternative therapies, perceptions of negative outcomes associated with steroid use, lack of support and guidance from health professionals regarding what to do with their asthma medications and the risks of poorly controlled asthma during pregnancy
[22]. Moreover, women overestimate the teratogenic risks of asthma medication especially the steroid medications, with one report citing women perceived a 42% teratogenic risk for oral corticosteroid versus 12% risk for inhaled corticosteroid
[23].

Prescribers have also been shown to be hesitant to prescribe and encourage use of asthma medications during pregnancy. Over a quarter of family physicians have said they would instruct their pregnant patients to decrease or discontinue asthma medication during pregnancy, when asthma was well controlled by current therapy
[9], potentially jeopardizing asthma control. Pregnant women are also less likely to be treated with systemic corticosteroids for acute asthma exacerbations than non-pregnant women (50.8% versus 72.4%)
[24].

The uncertainty and anxiety surrounding medication use and asthma control during pregnancy emphasise the crucial role of doctors, pharmacists and midwives in ensuring patient adherence to asthma medications during pregnancy and educating them on the risks of uncontrolled asthma during pregnancy. A collaborative approach between the pregnant women, doctors, midwives and pharmacists is needed to maintain adequate asthma control. Monthly monitoring has been recommended by guidelines
[25] to maintain optimal asthma control as different stages of pregnancy can have an effect on asthma control
[8]. We aim to test an intervention that allows for regular patient self-monitoring and a multidisciplinary health professional approach for asthma management during pregnancy; if successful it could justify funding for more support services for these women.

There also needs to be more detailed guidelines and objective measures for monitoring lung function for the treatment of pregnant women with asthma. The exhaled fraction of nitric oxide (FeNO) has been investigated as a marker for asthma control during pregnancy, but is expensive and not easily accessible
[26]. Forced Expiratory Volumes in one and six seconds (FEV_1_/FEV_6_) has shown to be effective in detecting airway obstruction in the elderly and could be helpful in pregnancy
[27]. FEV_1_/FEV_6_ may be a way of differentiating the shortness of breath associated with pregnancy from worsening asthma symptoms and a more convenient and affordable way of monitoring and guiding therapy in pregnant asthmatic women.

### Objective

To determine whether a multidisciplinary approach involving asthma education and regular monitoring during pregnancy will decrease asthma exacerbations with associated maternal and perinatal benefits. We hypothesis that the intervention group will have a better mean asthma control score than the control group at three and six months.

## Methods/design

### Study design

This is a single-blinded parallel-group randomized controlled pilot trial which will be conducted in the antenatal setting. It will test and evaluate a Multidisciplinary Approach to Management of Maternal Asthma (MAMMA©) which will involve education and regular monitoring by patients and their health professionals. The flow of the study design is outlined in Figure 
1. Recruited participants, stratified by disease severity, will be allocated to the intervention or the usual care group in a 1:1 ratio. Both groups will be followed prospectively throughout pregnancy, and outcomes will be compared between groups at three and six months from baseline to evaluate the effectiveness of this intervention.

**Figure 1 F1:**
[figure not shown]
Participant flow diagram.

### Inclusion and exclusion criteria

All pregnant women with asthma attending antenatal outpatient clinics who are in their first or second trimester, and who can communicate in English will be considered. Patients who are under the age of 18 years or who have not had asthma symptoms (wheeze, chest tightness and/or use of their reliever asthma medication) in the last year will be excluded. Participants who are also unlikely to meet the demands of the trial will be excluded (e.g. planning to relocate during the trial). Furthermore, participants who were previously involved in our previous qualitative exploratory study conducted at the same maternity hospital, titled “Asthma during pregnancy; the experiences, concerns and views of pregnant women with asthma”
[22] will also be excluded. Lastly, in the event of a miscarriage or termination of pregnancy, the participant will be excluded from the trial. Participant characteristics will be described in Table 
1.

**Table 1 T1:** Demographic and clinical characteristics of the study population at baseline

**Characteristic**	**Intervention group (n=30)**	**Control group (n=30)**
Patient information		
Age in years Mean [SD]		
Parity		
Gravidity		
Gestational age at first visit in weeks Mean [SD]		
Height in cm Mean [SD]		
Adherence Score Median [IQR]		
Ethnicity		
Australian		
Arabic		
Asian		
European		
Other		
Asthma severity^+^		
Intermittent to Mild		
Moderate to Severe		
Asthma medication		
SABA only		
ICS+SABA		
ICS/LABA + SABA		
FEV_1_ in litres Mean [SD]		
FEV_1_%predicted Mean [SD]		
FEV_1_/FEV_6_ Mean [SD]		
Co-morbidity		
Gestational diabetes		
Hypertension in pregnancy		
Anxiety/depression		
Other		
Smokers		
Health Care Concession Card holders		

ICS – inhaled corticosteroid, LABA- Long acting beta agonist, SABA – short acting beta agonist.

^+^Asthma severity classified by National Asthma Handbook
[28].

Values are given as number (percentages) unless specified.

### Recruitment

Participants will be recruited from antenatal clinics of two major Victorian women’s hospitals. Four recruitment methods will be used to ensure the sample size is reached efficiently:

1. Pregnant women who have self reported asthma will be approached at their antenatal outpatient appointment.

2. Advertisement posters publicising the trial will be placed in the outpatient department alongside an ‘expression of interest’ box where participants can leave their contact details. Study packs (including an explanatory statement with an expression of interest form and a reply paid envelope) will also be available in the outpatient department so potential participants can take the information home to read and post back expression of interest forms.

3. Midwives will also be asked to help identify eligible pregnant women with asthma during their first outpatient visit. They will be asked to approach any woman who has indicated they are asthmatic and hand them a study pack, which will be available in the outpatient department.

4. A list of pregnant asthmatic women who have had their first outpatient visit will be generated weekly from the medical records database which stores antenatal information for all hospital patients. Study packs will be posted to the women who are on the weekly list.

Written informed consent will be obtained from all participants. All participants will be over the age of 18 years and will have competency to consent. During the recruitment phase, each participant will be asked to nominate her preferred family physician (general practitioner) to be involved in the trial who will be the lead clinician responsible for her asthma management during pregnancy.

### Group allocation

Participants will be asked basic questions to determine their asthma severity in accordance with the National Asthma Council Management Handbook
[28] classifications. Participants will be stratified into two groups: mild intermittent asthmatics and moderate-severe persistent asthmatics. Within these two strata, block randomization using random blocks of four and six will be conducted using the sealed opaque envelope method. A random sequence of numbers will be generated using the Random allocation software program® by an external researcher who is not part of the research team. Only this researcher will be aware of the allocation sequence. Numbered envelopes will be opened by the leading investigator AL to allocate participants to the usual care group (UCG) or the multidisciplinary care group (MCG) at time of recruitment and will enrol the participant into the study. Stratification and block randomization are included to ensure a balance of asthma severities between groups and an even number of participants per group. Outcome assessors will be blinded to participant group allocation.

### Intervention (MCG participants)

The Multidisciplinary Approach to Management of Maternal Asthma (MAMMA©) intervention will embrace a collaborative approach involving the participant’s family physician, pharmacist and asthma educator. Details of the intervention are described in Figure 
2. Asthma education, monitoring, feedback and follow-up are integral components of the monthly intervention. Every month, participants in the intervention group will be contacted by the trial’s nominated pharmacist for an hourly session to assess their asthma control by administrating the Asthma Control Questionnaire (ACQ)
[29] and a short data collection form which inquires about oral corticosteroid use, asthma related hospital admissions, days off work and preventer to reliever use ratio. The ACQ states that an increase in a score of 0.5 is a clinically significant deterioration of asthma control
[29]. The trial pharmacist will provide feed back to the participant’s nominated family physician if the ACQ score has increased by 0.5 or greater and if there has been a documented exacerbation since the last monthly visit. The pharmacist and family physician will then collaborate on appropriate step up therapy for the participant. It is anticipated that this close monthly monitoring will maintain the participant’s asthma under closer control during pregnancy. Each participant in the MCG will be given a handheld device (PiKo-6) to use as they please for home monitoring of lung function and instruction in the use of PiKo-6. They will also receive pharmacist led medication management review at the beginning of the trial, periodic review of inhaler device technique by asthma educator, trigger avoidance and smoking cessation support (if relevant). The MCG will also have their FEV_1_/FEV_6_ measured monthly during the trial. Adherence and uptake of the intervention will be described in Table 
2.

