**Figure 2 F2:**
[figure not shown]
MAMMA© study design.

**Table 2 T2:** Adherence to intervention by intervention and control groups

	**Intervention group n(%)**	**Control group n(%)**
No. of reviews recommended by intervention pharmacist		
No. of asthma action plans up taken		
No. of recommended medication changes up taken		

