### Control (UCG participants)

The control group will receive usual medical care; this normally includes their regular antenatal visits ranging from weekly to monthly depending on trimester and other complications. They will not receive the intervention, any additional monitoring or education sessions like participants in the MCG. If during follow ups at three and six months, their asthma control becomes a concern (2 or more documented exacerbations without resolution (i.e. increasing preventer dose) since prior assessment or their ACQ score exceeds 2, the participant and their family physician will be notified (with participant permission). This notification will be taken into account when we do the analysis.

Both groups will be given a summarised version of the “Asthma and Healthy Pregnancy” brochure from the Asthma Foundation of New South Wales, Australia which is a pamphlet on basic asthma facts to avoid unfair disadvantage to participants in the control group and to minimise the risks of poorly controlled asthma.

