[30], a target range for FEV_1_/FEV_6_ measurements during pregnancy could be identified and prompt further research in using this ratio as a marker for asthma control during pregnancy. FEV_1_/FEV_6_ could be a simple and easier method of assessing asthma control and help prescribers better distinguish between asthma symptoms and the shortness of breath associated with pregnancy. Women will have the convenient option of monitoring their asthma at home using a handheld spirometer and adjusting therapy or management according to an individualised asthma action plan.

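### Read literally, the intervention arm's physician-feedback rule needs both an ACQ rise and an exacerbation, and as stated it has no trigger for a stable ACQ above 2

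*Protocol article*

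**What the plan says.** In the protocol article, the section Intervention (MCG participants) has the trial pharmacist administer the ACQ every month. Feedback to the family physician whom the woman has named is given under this condition: "if the ACQ score has increased by 0.5 or greater and if there has been a documented exacerbation since the last monthly visit". Just before this rule, the article says of the ACQ that "an increase in a score of 0.5 is a clinically significant deterioration of asthma control". The sentence just after the rule gives the consequence: "The pharmacist and family physician will then collaborate on appropriate step up therapy for the participant". The Recruitment section makes the nominated family physician the clinician in charge of the woman's asthma during pregnancy.

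The section Control (UCG participants) sets a separate rule for the three- and six-month follow-ups in usual care. Its first limb is two or more documented exacerbations without resolution. It continues: "since prior assessment or their ACQ score exceeds 2, the participant and their family physician will be notified (with participant permission". This rule uses an explicit 'or' and an absolute ACQ level, and it is stated for usual care only.

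**The concern.** The rule has two weaknesses.

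- **The connective.** 'And if' can mean that both conditions are required or that each is a separate trigger. Under the first meaning, a woman whose control has worsened by an amount the article itself calls clinically significant prompts no report unless she has also had an exacerbation.
- **The form of the trigger.** The only ACQ criterion is a rise. Poor control that is already present and does not worsen is invisible to it. The article regards an ACQ above 2 as a concern in usual care, but the text gives no matching prompt for the arm that is measured every month.

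Two things are at stake. The first is safety: joint step-up of therapy is described as following this feedback, and the Background links poor control in pregnancy to preterm birth, low birth weight and pre-eclampsia. The second is delivery: in a pilot of a care model meant for wider use, two pharmacists could apply this sentence differently to the same woman.

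**Working it through.** The article gives no computed figure on this point, so there is none to reproduce. The check applies the rule as written to each possible input.

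**Inputs from the article:** a rise threshold of 0.5 and a documented exacerbation (Intervention section); ACQ above 2 at three or six months, with permission (Control section). The ACQ values in the cases below are assumed for illustration. They are not frequencies, which the article does not allow one to derive.

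**Step 1: the two readings of the connective.**

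| ACQ rise of at least 0.5 | Exacerbation | 'Both' reading | 'Either' reading |
|---|---|---|---|
| no | no | no feedback | no feedback |
| no | yes | no feedback | feedback |
| yes | no | no feedback | feedback |
| yes | yes | feedback | feedback |

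The readings disagree in two of the four rows.

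**Step 2: a rise alone.** ACQ goes from 1.0 to 1.5 with no exacerbation. The change is 1.5 − 1.0 = 0.5, which meets the threshold. 'Both' gives no feedback; 'either' gives feedback.

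**Step 3: stable poor control.** ACQ stays at 2.5 with no exacerbation. The change is 2.5 − 2.5 = 0, below 0.5, so the woman is in the first row of the table at every monthly session. No feedback is triggered on either reading. Under the usual-care rule 2.5 > 2, so a woman with this score at a follow-up would, with permission, be notified together with her physician.

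**Step 4: slow worsening, which depends on a further assumption.** ACQ rises by 0.4 a month from 1.0, with no exacerbation: 1.0, 1.4, 1.8, 2.2, 2.6, 3.0, 3.4. If the rise is counted from the last visit, each change is 0.4, below 0.5, and the rise condition is never met. The usual-care rule would be met at month 3 (2.2 > 2) and month 6 (3.4 > 2). If the rise is counted from baseline instead, it reaches 1.8 − 1.0 = 0.8 by month 2 and the condition is met. This case is therefore weaker than Step 3, which holds under either way of counting.

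**Step 5: the proposed rule.** With an added limb of ACQ above 2, Step 3 triggers at each monthly session and Step 4 triggers from month 3 at the latest. With 'or', Step 2 triggers as well.

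**The case against.** The strongest reply has four parts.

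- **Figure 2.** The article refers to it for details of the intervention, and it is not available here. It may contain a level-based trigger, as may the full working procedures. This stands as a limit: the point can concern only the rule stated in the text.
- **Context favours 'either'.** The preceding sentence and the repeated 'if' suggest two separate triggers. That is probably what was meant. The literal wording still says otherwise, and the usual-care rule shows that the article writes 'or' when it means it.
- **Other routes exist.** Intervention women have monthly pharmacist sessions and a medication review at the start. Table 2 counts "No. of reviews recommended by intervention pharmacist" and "No. of recommended medication changes up taken", neither tied to the 0.5 rise. The Discussion foresees women "adjusting therapy or management according to an individualised asthma action plan". The Intervention section also lists feedback among its monthly components, without saying to whom. The rule does not say that feedback is given only in these circumstances. All this stands as partial mitigation; what remains missing from the text is a stated prompt to the physician.
- **The two rules serve different purposes.** The usual-care rule is a safety net for women who get no extra monitoring. A change-based rule on top of an entry review is a coherent choice. So different rules by arm are not in themselves a contradiction. The usual-care cut-off is used here only because it is the article's own marker of concern.

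A reader might also infer that the monthly form cannot identify an exacerbation, since it is described as "a short data collection form which inquires about oral corticosteroid use, asthma related hospital admissions, days off work and preventer to reliever use ratio". The article does not support that. The form is only summarised, oral corticosteroid use and admissions bear directly on exacerbations, and 'documented' may refer to other records.

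**Conclusion.** The point holds, as a minor one, with medium confidence. The literal rule requires two events where the article's own preceding sentence treats one of them as clinically significant. On either reading, the rule in the text prompts no physician feedback for a stable ACQ above 2 without an exacerbation. The second conclusion assumes that Figure 2 adds no level-based trigger. How many women would be affected cannot be derived from the article.

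A reader might go further and infer that the rule biases the comparison between arms, or that women in the intervention arm have no route to a change in therapy. Neither is supported. Nothing here shows an effect on the estimate of the ACQ difference, its analysis or the sample size, and the article describes other routes to treatment change. The point concerns safety and consistent delivery of the intervention.

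**What to change.** Reword the feedback sentence so that any one of three findings at a monthly session is enough for the trial pharmacist to contact the nominated family physician:

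1. ACQ up by at least 0.5;
2. a documented exacerbation since the previous monthly visit;
3. with the participant's permission, as in usual care, an ACQ above 2.

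If Figure 2 or the working procedures already contain an ACQ-level trigger, repeat it in this sentence so that the text and the figure agree.

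The cost is one sentence. The ACQ is already taken monthly and the cut-off is the article's own, so no new measurement or outside threshold is needed. The downside is some extra contacts for the pharmacist and family physicians, at most one per monthly session for a woman whose ACQ stays above 2.
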